## Abstract

**Background:** Parenting a toddler is a challenging experience for many parents with times of emotional dysregulation in both parent and child. Parenting interventions may be useful for parents to improve their ability to regulate emotions and respond to children’s emotions in a way that assists the child to understand and regulate emotions (emotion competence). *Tuning in to Toddlers* (TOTS) is a new parenting program that aims to improve parents’ emotion regulation, emotional responsiveness, and emotion coaching (aspects of emotion socialization) to promote optimal emotional development in toddlers, and prevent social and behavioral difficulties. This paper outlines the rationale, methodology, intervention, and recruitment used in a trial to establish program efficacy.

**Methods/Design:** Parents of toddlers aged 18–36 months old were recruited through child care centers (CC) and maternal child health (MCH) centers in Melbourne, Australia and were allocated to either intervention or a 15-month wait-list control condition in a cluster-randomized controlled design. Inclusion criteria were a child in the age range at baseline attending one of the CC or MCH centers. Exclusion criteria were if the parent/carer had insufficient English to attend the intervention and complete measures. Parents in the intervention condition participated in the 6-session group TOTS program delivered by two facilitators using a structured manual and measures of program fidelity and acceptability. Participants in the wait-list control condition received the intervention after a 15-month waiting period. Participants completed measures at baseline, post-intervention (intervention participants only) and 15-month follow-up. Primary outcome measures included parent emotion socialization (parent-report and observed). Secondary outcomes included parent-reported parent functioning (emotion regulation and mental health), toddler social, emotional and behavioral functioning, and parent and toddler systemic cortisol stress (using hair samples). The study was designed to comply with the CONSORT statement and intervention reporting outlined using TIDieR.

**Results:** Three hundred and six parents were recruited and completed baseline parent questionnaires, with a further 234 completing parent–child observation assessments, 235 parent cortisol, and 198 child cortisol.

**Discussion:** This paper is a methodological description of the TOTS randomized controlled trial evaluation protocol. It outlines some of the challenges in recruiting parents of toddlers to parenting programs.

**Clinical Trial Registration:**
www.ClinicalTrials.gov, identifier ACTRN12615000 962538.

## Introduction

The first 3 years of life are a critical and sensitive period for promoting children’s brain development (Sroufe, 1997), as well as their emotional competence (skills in understanding and regulating emotions; Denham, 1998). The parent–child relationship is central in facilitating all aspects of children’s functioning (Mahoney, 2009) and parent emotion socialization is one of the most established factors contributing to children’s emotional competence (Eisenberg et al., 1998). Emotion socialization includes parent’s own expressiveness, and their reactions to and coaching of children’s emotions (Eisenberg et al., 1998). For preschool- and school-aged children, emotion coaching parenting has been linked to better emotion knowledge, social skills and academic results, and fewer physical illnesses and behavior problems (Gottman et al., 1996, 1997; Johnson et al., 2017). Conversely, emotion-dismissing parenting (where parents avoid or are critical of children’s emotions) has been linked to deficits in children’s emotion knowledge and social skills, and more behavior problems (Eisenberg et al., 1998; Johnson et al., 2017). The toddler years are when the foundations for emotional competence are being laid (Denham, 1998), while also being a stressful, challenging time for parents as toddlers often express intense emotions as they strive for independence (Sroufe, 1997). The way parents manage their own emotions and how they respond to their toddler’s emotions is important for reducing stress, promoting optimal development and preventing problems in children (Mahoney, 2009). *Tuning in to Toddlers* (TOTS) is a new program teaching parents these skills but has not yet been evaluated using a randomized controlled trial to determine the impact of the program on parents and toddlers. The following study protocol outlines how TOTS will be evaluated in a randomized controlled trial and also addresses challenges in recruitment of parents of toddlers to a parenting program.

### Background

Central to positive developmental outcomes are parental responsiveness, warmth and sensitivity, combined with an absence of angry, irritable parental affect (Landry et al., 2000). To achieve key developmental milestones in the toddler years, parents need to balance providing boundaries for children’s exploration with being emotionally sensitive and attuned (Belsky and Fearon, 2002). Indeed, the development of an emotionally secure attachment early in life is crucial for healthy social, emotional and behavioral development, with long lasting consequences (Fraley, 2002). Secure attachments are created by countless interactions between parents and very young children within an environment of acceptance, acknowledgment and emotional attunement (van der Voort et al., 2014). Despite this evidence, many prevention or early intervention programs do not start until the preschool or school aged years when problems may have already emerged. There are few evidence-based group programs for parents of toddlers (see Barlow et al., 2016), and those that do exist either focus on changing children’s behavior or work with the parent–child relationship in clinical populations where there are attachment difficulties. Because an emotionally responsive parent–child relationship provides a solid protective base for optimal child development, it is important that early prevention efforts target the parent–child relationship in infancy/toddlerhood when this relationship is still forming. Caring for very young children can also be highly stressful for parents, resulting in greater reactivity in parents and more emotionally dismissive responses with their toddlers (Martorell and Bugental, 2006). Helping parents manage their stress, regulate emotions and parent effectively becomes an important target for prevention.

*Tuning in to Toddlers* (TOTS; [name] et al., 2017) is designed to teach parents skills that improve their capacity to manage stress, regulate their emotions, improve parent–child emotional connection, help children understand and regulate their emotions, and ameliorate behavior difficulties early (Sanson et al., 1993). TOTS aims to provide parents with skills in how to emotion coach their toddler; knowledge about toddler development; opportunities to explore automatic beliefs about emotions that may contribute to emotionally dismissive and/or harsh parenting; skills in responding to attachment and exploration needs in their toddler; strategies to help children learn to understand and regulate emotions; and skills in understanding and managing parents own emotions. The TOTS program was adapted from the evidence-based *Tuning in to Kids* parenting program ([name] et al., 2010). An initial pilot study of TOTS with 34 parents of 24- to 36-month-old children showed that post-intervention there were reported and observed improvements in parents’ use of emotion coaching and a reduction in emotion dismissing behaviors with medium to large effect sizes; parents also reported fewer toddler disruptive behaviors with small effect sizes (Lauw et al., 2014). Program attendance and satisfaction with the TOTS program was high and the greatest challenge was in recruitment of the target sample. The current study aims to use a randomized controlled design with a larger sample and a control group to more rigorously test whether the TOTS program is efficacious. Efforts to recruit through a number of avenues (childcare and maternal child health centers) were also used to explore whether this increased uptake and engagement.

The proposed study uses parent-report measures and direct observation of parent–toddler interactions to determine any changes in parenting including parent emotion regulation, emotion dismissing, emotion coaching, and harsh/warm parenting. In addition, biological measures of stress are also used to examine whether the intervention leads to reduced parent and toddler stress. Stress can be measured via assessing cortisol, a glucocorticoid hormone (Wells et al., 2014). The hypothalamic–pituitary–adrenal (HPA) axis is activated under stressful conditions releasing cortisol from the adrenal cortex (Staufenbiel et al., 2013). Usually stress has been measured using cortisol concentrations in saliva, blood and urine at a single time point (Wells et al., 2014), however, a newly established technique using hair cortisol concentrations provides a measure of retrospective chronic stress (Russell et al., 2012). While there are some mixed conclusions about the use of hair cortisol as a measure with very young children (Bryson et al., 2019), higher hair cortisol has been found to be associated with chronic stress including chronic pain, unemployment, shift work, serious life events, and psychopathology in adults (Staufenbiel et al., 2013). In order to examine whether TOTS reduced stress in parents and toddlers, the study included hair samples to measure systemic cortisol with the expectation that those in the intervention condition would have lowered parental and toddler stress after the program.

### Aims and Hypotheses

This paper outlines the research protocol and recruitment process being used to evaluate the efficacy of TOTS. This paper also describes the process of recruitment being used to obtain the sample while outlining strategies used to overcome barriers to engaging parents of young children in a parenting intervention. The primary outcome is change on the measures of parent emotion socialization, and the secondary outcomes are change on the measures of parent functioning (emotion regulation and mental health), toddler’s social, behavioral and emotional functioning, and systemic cortisol stress in parents and toddlers. It is hypothesized that based on the TOTS pilot study (Lauw et al., 2014), at 15-month follow-up we will see improved parent emotion socialization (reduced emotion dismissiveness and increased emotion coaching) in intervention participants but not control participants. It is also hypothesized that at 15-month follow-up we will see improved parent functioning (reduced emotion regulation difficulties, improved parent mental health) and reduced child behavior problems in intervention participants but not control participants. The impact of the program has not previously been examined with cortisol stress, however, if parents improve in skills regulating their own emotions and their responses to their toddler’s emotions after program participation, it is hypothesized that at 15-month follow-up there will be lower cortisol stress for parents and toddlers in the intervention condition (but not control).

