### Power Analyses

Using methods proposed by Eldridge et al. (2006), the estimated design effect for the study is 1.30 (based on 40 clusters of average size 7, a coefficient of variation for cluster size of 0.25, and a conservative at worst intra-class correlation of 0.05). The following power calculation incorporates this estimated design effect from clustering, and is done for feasible differential treatment effects at 15 months follow-up, where attrition will be highest. The treatment effect difference is conservatively estimated to result in group differences of about 0.40 SDs for continuous outcome measures. To achieve 80% power at a 5% significance, the required sample size at follow-up needs to be 100 × 1.30 = 130 participants in each condition. Based on our other studies, including our pilot study, we estimated there will be 10% attrition. This implies that 130/0.90 = 144 participants are needed in each condition for the study to have sufficient power.

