### Planned Statistical Analyses

Data will be analyzed using SPSS, beginning with data cleaning and assumption testing. Multiple imputation will be used to address missing data. A series of analyses are planned. First, independent samples *t*-test analyses will determine whether there are any systematic differences between pre-intervention scores for demographic and outcome variables for the intervention and the control conditions. Any baseline differences will be used as covariates in subsequent analyses. In addition, those with missing time 2 and 3 data points will be examined to determine differences from those completing follow-up assessment. Next, because parents are nested in centers, intraclass correlations will be computed to assess if center membership contributes to outcome variance. Our previous work has shown that kindergarten or school membership contributes from 8 to 11% of variance in child outcome variables (e.g., [name] et al., 2010; Wilson et al., 2012). Therefore, multilevel analyses using the mixed procedure in SPSS will be conducted to compare intervention and control participants across the different measures over time whilst considering the impact of the nested design (i.e., children attending different child care centers) and baseline covariates. Effect sizes will be calculated using Cohen’s *d*.

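### The primary comparison is framed as change, with baseline adjustment only when a t-test shows a difference; always adjusting the 15-month score for its baseline would be more precise

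*Protocol article*

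**What the plan says.** Aims and Hypotheses defines the endpoint: "The primary outcome is change on the measures of parent emotion socialization". The hypothesis in the same section is placed at the end of follow-up: "at 15-month follow-up we will see improved parent emotion socialization", in the intervention arm but not in the control arm.

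Power Analyses describes a calculation that "is done for feasible differential treatment effects at 15 months follow-up, where attrition will be highest". Its effect size is a treatment effect "conservatively estimated to result in group differences of about 0.40 SDs for continuous outcome measures". It does not say whether the SD is that of the score or that of its change, and no correlation between baseline and 15 months appears.

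Planned Statistical Analyses begins with t-tests of demographic and outcome variables at baseline, followed by the rule "Any baseline differences will be used as covariates in subsequent analyses". Multilevel models will then "compare intervention and control participants across the different measures over time", allowing for centers and baseline covariates. Missing data are to be multiply imputed. According to Study Design, the middle questionnaire goes to the intervention arm only, so baseline and 15 months are the only occasions that both arms share.

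**The concern.** An endpoint called change, analysed by comparing arms over time, points to a model in which baseline is the first response and the treatment effect is the arm-by-time term. With two common occasions, that term is the difference between arms in mean change. Two things follow.

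First, its variance depends on r and is never smaller than that of the 15-month score adjusted for baseline, so information already collected is not fully used.

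Second, an arm that happens to start worse tends to show more improvement through regression to the mean. The article's safeguard is to add baseline differences as covariates. If a baseline score is added as a plain main effect to a model where it is already a response, it does nothing to the arm-by-time term. The rule could then fail in the situation it is meant for.

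**Working it through.** **Inputs.** From Power Analyses: effect 0.40 SD, 80% power, 5% significance (two-sided assumed), design effect 1.30, 130 per arm at follow-up, 10% attrition. From Results: 166 intervention and 140 control parents. Assumed: r, equal SDs at both occasions, the same design effect for each contrast, and 0.40 as a raw-score SD.

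**1. The article's own figure.** A two-sample t-test with d = 0.40, 80% power and two-sided 5% needs 99.1 per arm, stated as 100. Then 100 × 1.30 = 130, and 130/0.90 = 144.4, stated as 144. The calculation reproduces. The effective size at follow-up is 130/1.30 = 100 per arm.

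**2. Variances, in units of the outcome variance.**
- Change: 2(1-r)
- 15-month score adjusted for baseline: 1-r²
- Ratio, adjusted to change: (1-r²)/[2(1-r)] = (1+r)/2, which is below 1 for every r below 1.

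**3. Power at 100 effective per arm.** The standardized effect is 0.40/√[2(1-r)] for change and 0.40/√(1-r²) for the adjusted score.

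| r (assumed) | Effect, change | Power, change | Effect, adjusted | Power, adjusted |
|---|---|---|---|---|
| 0.3 | 0.338 | 66% | 0.419 | 84% |
| 0.4 | 0.365 | 73% | 0.436 | 87% |
| 0.5 | 0.400 | 80% | 0.462 | 90% |
| 0.6 | 0.447 | 88% | 0.500 | 94% |
| 0.7 | 0.516 | 95% | 0.560 | 98% |

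If 0.40 is instead an SD of change, the change contrast has the stated 80% by construction and needs the same 99 to 100 per arm.

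**4. Shift given a chance baseline difference D (intervention minus control).** Change shifts by -(1-r)D, an unadjusted 15-month comparison by +rD, and the adjusted comparison by about 0. With 166 and 140 parents and clustering ignored, the standard error of D is √(1/166 + 1/140) = 0.115 SD.
- D just reaching p < 0.05 is about 1.96 × 0.115 = 0.23 SD. Change then shifts by 0.16 SD at r = 0.3 (40% of 0.40) or 0.11 SD at r = 0.5 (28%).
- D of one standard error gives 0.08 SD at r = 0.3 or 0.06 SD at r = 0.5.

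**5. What the covariate rule does.** A covariate that is constant over time and entered as a main effect moves a person's fitted values equally at both occasions, so it cancels from the within-person difference. In simulated complete data the arm-by-time estimate stayed equal to the raw difference in change (largest discrepancy 3e-15). If the covariate is also crossed with time, the estimate equals the baseline-adjusted 15-month comparison (discrepancy 1e-15). Multiple imputation produces completed datasets, so the complete-data result is the relevant one.

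**The case against.** A reader might infer that the 80% power belongs to a different endpoint. The documents do not support that. Under randomization the expected difference in change equals the expected difference at 15 months. The measures and the time point agree across sections, and the power section's wording also fits a between-arm difference in change. A shortfall needs a raw-score SD, r below 0.5 and unadjusted change together; the article states neither the SD basis nor r, and its model wording leaves the third open. At r = 0.5 the change contrast has the stated power, and above that it has more.

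A reader might also infer that change is biased or uniquely exposed to imbalance. It is not. The shift in step 4 is conditional on the observed D and averages to zero over randomization. Its variability is already inside the 2(1-r) variance, so it is not a second loss on top of the power figures. An unadjusted 15-month comparison shifts too, and by more than change when r exceeds 0.5.

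Finally, the article does not say how covariates enter the model. The rule is inert only without a time interaction, and that detail could sit in an analysis plan.

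All of this stands. It limits the point but does not remove it. The article itself fixes the endpoint as change and makes baseline adjustment conditional on a test, and neither choice makes the best use of a baseline that every participant provides.

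**Conclusion.** The point holds as a matter of efficiency and clarity, not as an error in the sample size. On the natural reading, the planned primary contrast is valid but less precise than the baseline-adjusted 15-month comparison at every r below 1. The gain from always adjusting is about 18 percentage points of power at r = 0.3, 10 at r = 0.5 and 3 at r = 0.7. Adjustment also removes the conditional shift from chance imbalance, which a main-effect covariate in the arm-by-time model would leave in place.

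These sizes rest on an assumed r, a raw-score SD, equal variances and a common design effect. Whether the trial falls short of 80% cannot be settled from the article.

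**What to change.** In Aims and Hypotheses and in Planned Statistical Analyses, define the primary comparison as the between-arm difference in the 15-month score from the multilevel model. Always adjust it for the same measure's baseline value, entered as a covariate and not as a response, whatever the baseline t-tests show. An equivalent is a repeated-measures model with the two arms' baseline means constrained equal. In Power Analyses, state that the 0.40 SD refers to the 15-month score.

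Change scores can remain as descriptive summaries. The cost is wording in three sections and one model specification, with no extra data or participants.

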## Materials and Methods

### Study Design

The study is a cluster randomized controlled design, with three data collection points. Pairs of child care (CC) centers and maternal child health centers (MCH) were matched based on location, socio-economic criteria (i.e., median house price in that area) and parent uptake rate after recruitment. These pairs were then randomized into one of two conditions: intervention or a 15-month wait-list control. A group-randomized design was used, as it is preferable when delivering an intervention to groups of parents to avoid contamination between intervention parents who attend the same center (Murray, 1998). In addition, this approach allows centers and parents to be blind to condition until after parents complete the baseline assessment battery. For all participants, the assessment battery included parent-report questionnaires, an observation assessment and parent and toddler systemic cortisol both at baseline and 15 months later. Intervention participants commenced TOTS within 1 month of the baseline assessment. Questionnaires were also administered immediately post intervention for intervention participants.

The study was designed to adhere with the CONSORT statement (Schulz et al., 2010) and the intervention is reported using guidelines outlined with TIDieR (Hoffman et al., 2014).

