#### Randomization Procedure

Cluster randomization was conducted by pairing centers based on the median house price in that location and the number of parents of the center completing baseline questionnaires. Then each “center pair” was randomly allocated to either intervention or control using a computer randomization program, Research Randomizer (Urbaniak and Plous, 2015). Parents were informed of their condition (intervention or control) following completion of the baseline assessment.

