Three hundred and twenty-two participants completed baseline questionnaires with 180 in the intervention condition and 142 allocated to the waitlist control condition. Of the 322 enrolled participants, 16 parents withdrew after completion of their baseline data. Of these, two were waitlist control parents (one did not wish to wait 15 months; the other had conflicting commitments in 15 months). Of the 14 intervention parents, two were excluded because they were assessed to be ineligible (e.g., not suitable for the parenting program due to high social anxiety *n* = 1; child too young *n* = 1). Seven parents did not attend any sessions (baby too unsettled *n* = 1, child care arrangements did not work out *n* = 3, unforeseen traumatic event *n* = 1, other commitments *n* = 2). Two intervention parents found the observation assessments stressful and did not wish to participate in the intervention. A scheduled daytime group did not go ahead due to low numbers and three of these participants were unable to attend an evening session. Instead they were sent a DVD and program booklet and were offered the program at a future date.

The final sample was 306 participants (166 intervention and 140 waitlist control), of which 241 were recruited from CC and 65 from MCH centers. Observation assessments were conducted with a random selection of 246 parent–child dyads at baseline (as mentioned earlier this was due to funding constraints). Hair cortisol concentration data was collected for 235 parents who attended the assessments and for 201 toddlers at baseline. Hair samples were not taken from 11 parents due to them choosing not to give a hair sample and from 34 toddlers due to parents not wishing the hair sample to be taken or due to toddler’s being distressed at receiving a haircut (some had never had a haircut before). There were no significant differences between those participants who completed the questionnaires only and those who completed the full assessment battery (including questionnaires, parent–child assessment and cortisol stress measures).

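### The text allocates matched pairs of centres, not centres within pairs, and neither the sample size nor the planned model takes account of the pair

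*Protocol article*

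**What the plan says.** Two sections of the protocol article describe the allocation. Study Design gives the unit allocated: "These pairs were then randomized into one of two conditions: intervention or a 15-month wait-list control". On how the pairs were formed, it says that they "were matched based on location, socio-economic criteria (i.e., median house price in that area) and parent uptake rate after recruitment". The Randomization Procedure section, which names house price and the count of parents with baseline data as matching factors, also makes the pair the unit: "Then each “center pair” was randomly allocated to either intervention or control".

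The Power Analyses section takes the centre as the independent unit. Its design effect of 1.30 is "based on 40 clusters of average size 7, a coefficient of variation for cluster size of 0.25". The ICC used there is 0.05, described as a worst case. Pairing plays no part in the calculation.

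The Planned Statistical Analyses section computes intraclass correlations for centre membership. It then fits multilevel models "whilst considering the impact of the nested design (i.e., children attending different child care centers) and baseline covariates". The pair is not named. The matching factors are not named either; one could enter only through the rule that variables found to differ at baseline become covariates.

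**The concern.** Matching centres serves a purpose when the members of a pair go to opposite arms, because what they share then cancels out of the treatment comparison. Read literally, both sections send the pair as a whole to one arm. What the two centres share (area, house price, uptake) would then be added to the treatment comparison rather than removed. The matching would balance nothing between arms, and 40 planned centres would make only 20 randomised units.

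At stake are the unit of inference, the degrees of freedom and the standard error of every outcome comparison. A model with centre as its only random level treats centres as independent within an arm and between arms. If whole pairs were allocated, the first assumption fails. If allocation was within pairs, the second fails, in the conservative direction. A reader of the article cannot tell which applies.

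**Working it through.** **Inputs from the Power Analyses section:** 40 clusters, mean size m = 7, coefficient of variation (CV) of cluster size 0.25, ICC 0.05, effect 0.40 SD, 80% power, 5% significance (taken here as two-sided), 130 per arm at follow-up, 10% attrition.

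**Input not in the document:** the correlation ρ between parents in the two centres of a pair. I assume a range of 0 to 0.05. The upper end makes parents in two paired centres as alike as parents in the same centre.

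**1. The plan's own figure.** For 0.40 SD at 80% power, about 99 per arm are needed without clustering; the plan uses 100. The design effect is 1 + (7 − 1) × 0.05 = 1.30, so 100 × 1.30 = 130. Then 130/0.90 = 144.4, stated as 144. The plan's figure is reproduced, with 40 independent centres as the units. Including the stated CV gives 1 + (7 × 1.0625 − 1) × 0.05 = 1.32, a small difference.

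**2. If whole pairs were allocated.** Each parent shares an arm with 6 others from the same centre (correlation 0.05) and 7 from the partner centre (correlation ρ):

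Design effect = 1 + (m − 1) × 0.05 + m × ρ

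Power (normal) = Φ(0.40 × √(130 / (2 × design effect)) − 1.96)

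| ρ (assumed) | Design effect | Needed per arm at follow-up | Power at 130 per arm, normal | Power, t test on 18 df |
|---|---|---|---|---|
| 0 | 1.30 | 130 | 81% | 76% |
| 0.025 | 1.30 + 0.175 = 1.475 | 148 | 76% | 71% |
| 0.05 | 1.30 + 0.35 = 1.65 | 165 | 71% | 66% |

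The 18 df are 20 pairs less 2. With the CV included in both, the design effect runs from 1.32 to 1 + (14 × 1.0625 − 1) × 0.05 = 1.69.

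A centre-only model at the planned ICC uses 1.30 where up to 1.65 applies. Its standard error is then √(1.30/1.65) = 0.89 of the correct one at the upper end. The nominal 5% test has a true error rate of 2 × (1 − Φ(1.96 × 0.888)), about 8%. At ρ = 0 there is no distortion.

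**3. If one centre of each pair went to each arm.** The shared part cancels:

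Design effect = 1 + (m − 1) × 0.05 − m × ρ

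| ρ (assumed) | Design effect | Power at 130 per arm, normal | Power, t test on 19 df |
|---|---|---|---|
| 0 | 1.30 | 81% | 77% |
| 0.025 | 1.125 | 86% | 82% |
| 0.05 | 0.95 | 91% | 88% |

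A model without the pair still works with 1.30. Its test is valid but conservative for ρ above 0, and the gain in these rows is not realised.

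**4. If centres were smaller than planned.** The Results section gives an average of 65 toddlers per child care centre and 4.6% uptake: 65 × 0.046 = 3.0 parents per centre, at the stage of expressing interest. With m = 3 and whole pairs allocated, the upper-end design effect is 1 + 2 × 0.05 + 3 × 0.05 = 1.25, or 1 + (6 × 1.0625 − 1) × 0.05 = 1.27 with the CV. Both are below the planned 1.30. The planned power would then not be lost from this source, although a centre-only model, which would use 1 + 2 × 0.05 = 1.10, would still understate the standard error.

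**The case against.** The strongest reply is that this is loose wording for an ordinary matched-pair design. The Strengths and Limitations section describes randomisation of centres as opposed to individuals. The Results section speaks of a parent's centre having been matched and randomised, and the power calculation counts 40 clusters. All of this fits allocation of centres within pairs, which is also the reading that gives the matching a purpose. This stands as a reason not to assert that pairs were the unit. It does not remove the problem, since none of these places describes a one-per-arm split and the two sections written to describe the allocation both say otherwise.

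A reader might infer from the arm sizes, "with 180 in the intervention condition and 142 allocated to the waitlist control condition", that whole pairs were allocated, because centres paired on parent numbers should give closer totals. The documents do not support that inference. The text gives neither the number of centres randomised nor the differences within pairs, and parent numbers were only one of the matching factors. With 20 pairs, a gap of 38 would need a typical within-pair difference of about 38/√20 = 8.5 parents; with more pairs a smaller difference would do. The split leaves the question open.

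It can also be said that the exact random-effect levels belong in an analysis plan that is not shown, and that keeping or breaking the match is a recognised trade-off because pair terms use degrees of freedom. Both points are fair. However, an analysis plan cannot correct the allocation statements, and the article does commit itself on the unit counted for power and on the nesting modelled.

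**Conclusion.** The point holds in a conditional form. Both allocation statements make the matched pair the unit, nothing in the article states a within-pair split, and the pair is absent from the sample size and from the described model. Under either reading the analysis does not follow the structure that was randomised.

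The consequence depends on what was done. If whole pairs were allocated, standard errors are too small whenever paired centres are correlated: at the planned size of 7, the design effect is 1.30 to 1.65 and power at 130 per arm about 81% to 71% (about 76% to 66% on 18 df). That range rests on the assumed ρ of 0 to 0.05 and on the planned cluster size; the loss is nil at ρ = 0 and smaller with smaller centres. If one centre per pair went to each arm, the centre-only model remains valid, tends to be conservative and forgoes the precision bought by matching.

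It would go too far to conclude that the randomised units were in fact halved, or that inference is invalid under both readings. The text is compatible with a conventional design badly described, and under that design the fault is one of wording and efficiency.

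**What to change.** 1. Check the allocation log. Correct the Study Design and Randomization Procedure sections so that both state which unit was allocated and how, and report the number of pairs and of centres in each arm.
2. If one centre of each pair went to each arm, add pair (the matching stratum) to the outcome models, with centre nested within pair.
3. If whole pairs were allocated, make pair the top random level, base the degrees of freedom on the number of pairs, and restate the design effect and power with pair sizes.

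The cost is a text correction, one further model term and a few degrees of freedom. The pairs were formed in order to randomise, so the identifiers already exist and no new data are needed.
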